#### Other outcome variables

Several other factors (e.g. confounders, effect modifiers) that may have an effect on the outcome of the intervention are defined as follows: Satisfaction with the intervention and / the process leading to the well-informed decision for both the patient and the invitees, the number of invitees, the relationship of the invitee to the patient, the duration of the meeting, the use of an interpreter, the number of visits necessary for the intervention, the treatment adherence of the professionals and the satisfaction of the professionals. These outcomes are recorded by the educators on a questionnaire for each intervention.

##### Product evaluation

Patients and invitees will be asked four questions on their opinion of the intervention provided by the educators: satisfaction regarding the educational intervention (e.g. usefulness, clarity). For example, *‘How satisfied are you with the clarity of the received information ’ (1 = very dissatisfied - 5 = very satisfied).*

##### Process evaluation

Patients and invitees will be asked eight questions on their opinion and satisfaction regarding the way in which the intervention is delivered. (e.g. logistics, cooperation, understanding, professionalism). The questions asked are based upon the concepts and the structure of the Revised Treatment Adherence Measure (TAM; [39,40]. The main underlying question of the TAM is: ‘Did the health care providers do what they were ought to do in congruency with their protocol?’ For example, *‘The researchers encouraged communication between me and my family/friends’ (1 = not at all - 5 = to a large degree).*

##### Educator process evaluation

This questionnaire (12 items) will be completed by the co-educator to determine whether the intervention was able to reach the right audience (reach) and whether it was implemented as intended (fidelity) [41]. For example, *‘How satisfied are you with the communicative aspects of the home visit?’ (1 = very dissatisfied - 10 = very satisfied).* Followed by, *‘What went well and what could have been improved?’ (open questions).*

#### Background variables

Socio-demographic data: date of birth, gender, education, employment status, marital status, number of children, ethnicity and religion will be collected through medical records. Medical data: medical diagnosis, history of other RRT’s, current treatment, date of first dialysis and blood type.

#### Sample size calculation

An *alpha* of .05 and a *power* of .80 was used in the following calculations, as proposed to be appropriate for behavioural research [42]. To determine an adequate sample size for detecting the effect we did a power analysis based on the proportion of LDKT’s performed in the control versus the experimental group in previous research [17]. We used this parameter since this is the only one on which there has been reported in the literature with regard to the current study parameters. Moreover the other parameters would reveal inconsistent sample estimates. For example, the knowledge parameter would show a large effect size which would result in a very low sample size whereas, self-efficacy would require a lager sample size. The required sample sizes to achieve a nominal power of 1-γ = 0.8 on a two-sided test with a α = 0.05 using a Fisher distribution revealed that at least 78 patients are required per study group to enable statistical judgments that are accurate and reliable. Calculations were performed in SAS; Power and Sample Size version 3.1.

#### Statistical analysis

Following the updated CONSORT statement [43], for this study the intention-to-treat population is defined as all randomized patients who are known to have received at least one home visit and who provide data for at least one post-baseline measurement for one or more of the key efficacy variables: no patient will be excluded for protocol violations which occurred during subsequent follow-up (modified intention-to-treat) [44]. Additional effort will be exerted by the educators to ask the drop-out patients to complete the post-measurement for the primary outcome.

For comparing the patients’ baseline-variables between the two research conditions the two tailed t-test for independent samples for the continuous variables, the two-tailed Mann–Whitney U-tests for the ordinal variables and the Chi-square tests for the categorical variables will be used. The effectiveness of our home-based educational intervention for the primary outcome variables will be analyzed with mixed modeling, i.e. multilevel regression modeling. The additional value of this multilevel testing lies in the flexibility to model individual growth trajectories and to handle missing data. The latter will only hold if structure of the missing data is Missing Completely At Random (MCAR) or Missing At Random (MAR), but not if the data turns out to be Missing Not At Random (MNAR). This technique is appropriate since missing data and drop-outs are inevitable in longitudinal research. Moreover, missing data affects study power simply by the reduced availability of data points [45]. We will strive to firstly minimize missing data, and to subsequently take this into account during analysis. The methodology of mixed modeling for repeated measures allows us the use of flexible error variance-covariance structure. Additionally, the predictive value of the baseline-parameters (main-outcome variables) on effectiveness can be estimated.

Finally, semiparametric regression analysis will be employed using Cox Proportional Hazard Model to examine the significance of the contingency between the hazard for an event of the experimental and control group on the secondary outcome variables. This model enriches the analysis by incorporating covariates in the regression equation (e.g. age, gender, ethnicity, dialysis time). Time-to-event graphs will be depicted for the experimental and control group separately. Patients with a LDKT will be regarded as having the ‘event’ whereas patients who continue dialysis during the follow-up period will be censored. DDKT is modeled as a competing event and therefore patients who take-up this treatment will also be censored.

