### Design & procedure

In this prospective RCT all patients will be invited to participate by the educators after the consultation with the transplant nephrologists. During the face-to-face informational consultation the patient will receive written and verbal information on the aims and procedures of the study. Spouses, relatives or friends accompanying the patient to the hospital may be present during this consultation. Our target is to include 80 patients of Dutch origin and 80 patients of non-Dutch origin in the study over a period of two years in order to compare effectiveness of the intervention among these two groups. With respect to the inequality in LDKT, patients of non-Dutch origin will inherently be overrepresented in the study. After informed consent is obtained, patients will be randomized to either the control or the experimental group. The control group will receive standard care. The experimental group will receive standard care plus a home-based educational intervention. In the face of the equity principle, we will provide all the study materials (e.g. brochures, questionnaires) in the six most common foreign languages in the Rotterdam municipality namely, English, Arabic, Turkish, Papiamento, Portuguese and Modern Hindi [29].

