#### Control condition

Patients assigned to the control group will receive standard care only. In the standard care all patients visiting our pre-transplantation outpatient clinic receive a consultation with a transplant nephrologist, a transplant coordinator, and a social worker. Additional to this verbal information, the patients receive a variety of written educational material and a DVD regarding various living donation and transplantation programs. All materials are translated in the six afore mentioned foreign languages. They can study this material in the coming four weeks before their second visit to the outpatient clinic during which they have the opportunity to ask additional questions. Additionally, our patients are invited to attend 4–6 times a year informational meetings held in the various regional hospitals. The baseline and post-measurements will be either handed out by the educators during the hospital visit or sent via mail. If necessary the educators may help in completing the questionnaire. The questionnaires are also available in six languages.

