#### Secondary outcome measures

Secondary outcomes are operationalized in terms of behaviour that may lead to LDKT or LDKT itself. This is divided into three categories: the number of applications for LDKT evaluation, the number of actual evaluations for LDKT, and the number of LDKT’s. These outcomes will be monitored using the patient’s medical records during the year following the intervention date. Furthermore, we will also monitor the timeframe between the intervention and the moment that the event arises (time-to-event).

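### The modified intention-to-treat population requires a home visit that only the experimental arm can receive, so as applied it selects patients after randomisation in one arm

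*Protocol article*

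**What the plan says.** The Statistical analysis section opens: "Following the updated CONSORT statement [43], for this study the intention-to-treat population is defined as" and continues "all randomized patients who are known to have received at least one home visit and who provide data for at least one post-baseline measurement" on at least one key efficacy variable. The sentence then adds that protocol violations during later follow-up lead to no exclusion, and ends by calling the set modified intention-to-treat. The article defines no other analysis set.

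The arms are described under Design & procedure and the two condition headings:

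- Allocation: "After informed consent is obtained, patients will be randomized to either the control or the experimental group". It comes before any session.
- Experimental arm: "The experimental group will receive standard care plus a home-based educational intervention". The baseline questionnaire is completed at the start of Session One (Experimental condition).
- Control arm: "Patients assigned to the control group will receive standard care only". Their baseline and "post-measurements will be either handed out by the educators during the hospital visit or sent via mail".

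On incomplete data, the Statistical analysis section says: "Additional effort will be exerted by the educators to ask the drop-out patients to complete the post-measurement for the primary outcome".

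The secondary outcomes are applications for LDKT evaluation, actual evaluations and transplants. Of these the article says: "These outcomes will be monitored using the patient’s medical records". The follow-up year is counted from the date of the intervention.

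**The concern.** Membership of the analysis set depends on an event that follows randomisation and can occur in only one arm. A patient randomised to the experimental group who withdraws, falls ill or is otherwise never visited leaves the analysis. The same kind of patient in the control group cannot be identified and stays. The comparison is then between experimental patients who took up the intervention and all controls with post-baseline data, and randomisation no longer protects it.

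The second condition, having post-baseline data, is different. It applies to both arms, so it is not one-sided, but it is a further selection made after randomisation.

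The definition is the only one in the article, so it appears to govern both the questionnaire comparisons (primary) and the LDKT comparisons (secondary).

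**Working it through.** **Step 1. Apply the definition to each arm.**

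| Condition | Experimental arm | Control arm |
|---|---|---|
| Randomised | yes | yes |
| At least one home visit | possible | not possible: standard care only, questionnaires at the hospital or by mail |
| At least one post-baseline measurement | possible | possible |

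Read literally, the number of qualifying controls is 0. Read as applying to the experimental arm only, the visit condition removes never-visited experimental patients and nobody from the control arm.

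**Step 2. Effect on numbers.** The target is 160 patients. The article does not state the allocation ratio; 1:1 is assumed, giving 80 per arm. With a share *f* never visited, the experimental arm keeps 80 × (1 − *f*): 76, 72, 68 or 64 for *f* = 5, 10, 15 or 20%. The stated requirement is 78 per study group, so the arm falls short once more than 2 of 80 (2.5%) are removed. The 78 itself is not disputed here. It cannot be reproduced, because the article does not give the two proportions behind it.

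**Step 3. Illustration of bias with no true effect.** The article gives neither the share never visited nor any event risk for this purpose, so all inputs are assumptions: 80 randomised per arm, overall risk *p* = 0.30, share *f* never visited, and risk *r* × *p* among them.

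Rate among the visited = (*p* − *f* × *r* × *p*) / (1 − *f*)

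Example, *f* = 0.20 and *r* = 0: 0.30 / 0.80 = 0.375, an apparent risk ratio of 0.375 / 0.30 = 1.25.
Example, *f* = 0.20 and *r* = 0.5: (0.30 − 0.20 × 0.15) / 0.80 = 0.3375, a ratio of 1.125.

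The type I error is the exact binomial probability that a nominal two-sided 5% test rejects, with 80 controls against 80 × (1 − *f*) visited patients.

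| *f* | Visited n | *r* | Rate among visited | Apparent risk ratio | Chi-square | Fisher |
|---|---|---|---|---|---|---|
| 5% | 76 | 0.5 | 0.308 | 1.03 | 5.2% | 4.2% |
| 5% | 76 | 0 | 0.316 | 1.05 | 5.6% | 4.7% |
| 10% | 72 | 0.5 | 0.317 | 1.06 | 5.9% | 4.5% |
| 10% | 72 | 0 | 0.333 | 1.11 | 7.7% | 6.0% |
| 15% | 68 | 0.5 | 0.326 | 1.09 | 6.0% | 5.5% |
| 15% | 68 | 0 | 0.353 | 1.18 | 10.0% | 9.2% |
| 20% | 64 | 0.5 | 0.338 | 1.13 | 8.0% | 6.2% |
| 20% | 64 | 0 | 0.375 | 1.25 | 16.3% | 13.0% |

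With nobody removed (80 v 80), the chi-square test rejects in 5.1% and Fisher's test in 3.3%.

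**Step 4. Sensitivity.** Varying the overall risk from 20% to 40% (normal approximation), 20% never visited with no events shifts the difference by +5 to +10 percentage points, with a type I error of about 11% to 22%. At half the average risk the shift is +2.5 to +5 points and the error about 6.6% to 9.3%.

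The sign depends on *r*. If never-visited patients had 1.5 times the average risk, *f* = 0.20 would give (0.30 − 0.20 × 0.45) / 0.80 = 0.2625, a ratio of 0.875, against the intervention.

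**The case against.** Several objections have force.

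- **A reader might infer that the trial would be analysed without controls.** That is not what the authors intend: the same section compares the two research conditions, and the Cox model is specified for the experimental and control groups. The literal reading shows faulty drafting. The substantive problem is exclusion in one arm.
- **The authors call the set modified intention-to-treat** and keep patients with later protocol violations. This discloses the departure. It does not repair a condition that one arm cannot meet, and it protects patients only once a visit has taken place.
- **A reader might infer that the rule contradicts the chasing of drop-outs and the use of a mixed model.** Neither follows. The chase fits patients who leave after a first visit, and nothing says that never-visited patients are pursued and then discarded. A mixed model can still handle missing data within the set.
- **A reader might infer that the bias is known to favour the intervention.** It is not. Randomisation follows information and consent, so some unwilling patients will have left beforehand. Practical considerations allows sessions at another location, which reduces refusals to host but also leaves unclear what counts as a home visit. Illness, an early deceased donor transplant or a donor found before the visit could move the bias either way.
- **The illustration is not the planned analysis.** It uses a binary test; the plan uses mixed models and a Cox model. Nothing in it quantifies bias in the questionnaires, and Fisher's test, which the sample size was based on, gives smaller figures.
- **Deleting the visit condition is not enough.** A never-visited experimental patient has no baseline as the procedure stands, and no intervention date from which to count follow-up. No such date is given for controls either. This stands, and the fix has to deal with it.

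**Conclusion.** The definition is wrong as written and should be changed. Its visit condition has no counterpart for controls and, applied as presumably intended, breaks the randomised comparison. This rests on the text alone and needs no assumption.

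The size and direction of bias are not established. Under the assumptions shown (no true effect, 80 per arm, 30% risk, chi-square test), the type I error is about 6–8% with 10–20% never visited at half the average risk, and about 8–16% if they have no events. At 5% never visited the inflation is negligible. If nearly every experimental patient is visited, the practical harm is small, but the plan cannot assume that in advance.

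**What to change.** 1. Define the primary analysis set as all randomised patients in the arm to which they were allocated, with no home-visit condition.
2. Fit the mixed model to all available questionnaire data. Where possible, collect the experimental arm's baseline independently of Session One, at the hospital or by mail as for controls, so that a never-visited patient still has one.
3. Analyse the medical-record outcomes for every randomised patient, from a time origin common to both arms such as randomisation, in place of the intervention date.
4. Keep the visited patients only as a per-protocol sensitivity set, labelled as such and not as intention-to-treat, and state whether a session held away from home counts as a visit.

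Cost: a reworded definition, a small change to baseline collection and a changed follow-up start date. The estimated effect may be slightly diluted because experimental patients who received no session are counted.

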## Background

Patients with end-stage renal disease have various options for renal replacement therapy (RRT): hemodialysis, peritoneal dialysis, deceased donor kidney transplantation (DDKT) and living donor kidney transplantation (LDKT). Although dialysis is a life-saving treatment, the patient is faced with a substantial loss of quality of life and a significantly increased risk of morbidity and mortality [1]. At least one quarter of the patients die on the wait list for DDKT [2]. The calculation of the time spent on the wait list for a DDKT starts on the first day of dialysis and is on average three to five years in the Netherlands [3]. Research shows that LDKT is associated with significant patient and graft survival benefits when compared to DDKT [4]. One of the benefits of early LDKT is avoiding or minimising time on dialysis. However, one of the main concerns among patients is the health of the living donor. Studies have shown that among healthy screened individuals, the health risks for the donor are limited [5]. The donor is usually admitted for 3–4 days for the nephrectomy, can resume preoperative social and professional activities within four to six weeks and in general the perceived quality of life remains the same [5,6]. LDKT rates have steadily been increasing and now exceed those of DDKT in the Netherlands [3]. However, there appears to be an inequality in access to the LDKT program between Dutch and the non-Dutch patients. In our center 44% of patients on the wait list for DDKT are from non-Dutch descent [7]. However, non-Dutch patients represent only 18% of the patients transplanted via the LDKT program (period: 2000–2010). Therefore, fewer non-Dutch than Dutch benefit from the advantages of LDKT. This inequality is also present in other western countries [8-10]. This health care inequity needs to be addressed [11,12]. This discrepancy is partly attributable to medical, socio-economic and ethnic factors, which exert an independent significant influence on the chance of receiving a LDKT [7]. Due to an accumulation of unfavourable factors in the non-European population, their chances for a LDKT dropped to only 10% compared to the reference population (69%) [13]. Of the socio-economic hurdles, health insurance is less relevant in the Netherlands due to a health insurance system which is accessible for all Dutch citizens. Other possibly contributing factors to this inequality are potentially modifiable psychosocial (e.g. patient education, cognitions and emotions) and culture-specific factors (social influences, communication attitudes) [14,15]. The Kidney Team At Home-study focuses on addressing those potentially modifiable factors in a home-based educational intervention.

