## Methods and design

### Study population

#### Patients

Eligible candidates are end-stage renal patients who have been referred to the pre-transplant clinic and are currently listed on the wait list for a DDKT and who do not have a potential living donor yet. This includes patients (>18 yrs) newly referred for transplant preparation as well as patients who are already listed. Patients who are mentally incapable (e.g. mental deterioration, schizophrenic) or those with a compromised medical condition who are unable to withstand the intervention will not be included.

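### Censoring at DDKT supports a cause-specific hazard ratio, but graphs drawn under the same rule as one minus Kaplan-Meier would overstate the proportion of patients who reach LDKT

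*Protocol article*

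**What the plan says.** The Protocol article, Secondary outcome measures, names three outcomes: applications for LDKT evaluation, actual evaluations, and LDKTs. Their timing is also recorded. On follow-up it says: "These outcomes will be monitored using the patient’s medical records during the year following the intervention date".

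The Statistical analysis section gives the method for these outcomes: "semiparametric regression analysis will be employed using Cox Proportional Hazard Model". The event rule is: "Patients with a LDKT will be regarded as having the ‘event’ whereas patients who continue dialysis during the follow-up period will be censored". It continues: "DDKT is modeled as a competing event and therefore patients who take-up this treatment will also be censored". On display it says: "Time-to-event graphs will be depicted for the experimental and control group separately".

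The rule covers LDKT, continued dialysis and DDKT. It does not mention death. The article names no estimator for the graphs and no cumulative incidence or subdistribution method.

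Two other sections show how common competing events may be. Under Patients, those eligible are "currently listed on the wait list for a DDKT and who do not have a potential living donor yet". The Background says the DDKT wait "is on average three to five years in the Netherlands", counted from the start of dialysis, and that "At least one quarter of the patients die on the wait list for DDKT".

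**The concern.** The difficulty is the inference in the sentence on DDKT, which presents censoring as the consequence of treating DDKT as a competing event. For a hazard comparison this works: a Cox model for LDKT that censors at DDKT estimates the cause-specific hazard ratio. For an absolute proportion it does not. Kaplan-Meier assumes that a censored patient could still have the event later at the same rate as those who remain at risk. A patient who has received a deceased donor kidney has left that risk set. One minus Kaplan-Meier therefore describes LDKT in a hypothetical setting without DDKT.

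The secondary research question concerns access, that is, how many patients actually go on to LDKT. A reader will take the height of the curve at 12 months as that proportion. If it is drawn under the stated censoring rule, it will be too high in both arms, and the absolute gap between the arms will look somewhat larger than it is.

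**Working it through.** **The plan's own figure.** The article gives no LDKT curve or 12-month percentage, so there is none to reproduce. Its sample size (at least 78 per group) rests on LDKT proportions from an earlier trial that the article does not state. This point does not depend on it.

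**Inputs.**
- Follow-up: 1 year (Secondary outcome measures).
- DDKT hazard *d*: the Background gives an average wait of 3 to 5 years. Read as the mean of an exponential distribution, this gives 1/5 = 0.20 to 1/3 = 0.33 per year. The constant hazard is an assumption.
- Death hazard *m*: the Background gives at least 25% dying on the wait list, without a period. Spread over 5 or 3 years, this is -ln(0.75)/5 = 0.058 or -ln(0.75)/3 = 0.096 per year. The spread is an assumption. Zero is the lower bound, for when deaths add nothing to the censoring.
- One-year LDKT as read from the curve: not in the article, so a range of 10% to 50% is assumed.

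**Formulas**, with LDKT hazard *l* and competing hazard *c* = *d* + *m*, at 1 year:
- One minus Kaplan-Meier, competing events censored: 1 - exp(-*l*), so *l* = -ln(1 - curve value).
- Actual proportion (cumulative incidence): *l*/(*l* + *c*) × (1 - exp(-(*l* + *c*))).

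**Worked example.** Curve value 30%: *l* = -ln(0.70) = 0.357. With *c* = 0.20, the cumulative incidence is 0.357/0.557 × (1 - exp(-0.557)) = 0.641 × 0.427 = 27.4%. The curve is 2.6 points too high, a ratio of 1.10.

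**Results** (actual LDKT proportion; excess of the curve in points; ratio of curve to actual):

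| Curve reads | *d* 0.20, *m* 0 | *d* 0.33, *m* 0 | *d* 0.20, *m* 0.058 | *d* 0.33, *m* 0.096 |
|---|---|---|---|---|
| 10% | 9.1%; 0.9; 1.10 | 8.5%; 1.5; 1.17 | 8.8%; 1.2; 1.13 | 8.2%; 1.8; 1.23 |
| 30% | 27.4%; 2.6; 1.10 | 25.8%; 4.2; 1.16 | 26.7%; 3.3; 1.13 | 24.7%; 5.3; 1.21 |
| 50% | 45.8%; 4.2; 1.09 | 43.3%; 6.7; 1.15 | 44.7%; 5.3; 1.12 | 41.7%; 8.3; 1.20 |

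**Difference between arms.** Suppose the competing hazard is the same in both arms and the curves read 10% and 30%. The apparent gap is 20 points. The actual gap is 18.3 points at *c* = 0.20, and 24.7 - 8.2 = 16.5 points at *c* = 0.429. For curves reading 30% and 50%, the actual gap is 18.5 and 17.0 points.

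**The case against.** Several parts of the case for leaving the text alone are sound.

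- **The Cox model.** A reader might infer that censoring at DDKT contradicts competing-risk modelling and makes the Cox analysis wrong. It does not. The stated aim is to compare hazards between arms, and censoring at the competing event is standard for a cause-specific hazard ratio. Only the label is missing.
- **The graphs.** The article never names Kaplan-Meier. If cumulative incidence curves are intended, the overstatement disappears. This stands as a limit, so the point is conditional. However, the only rule stated for these data is censoring, and the curve that follows naturally from it is the biased one.
- **The counts.** LDKTs are also counted from medical records over a fixed year. Apart from loss to follow-up, that count per arm gives the actual proportion without this bias. This stands: the point concerns the graphs and any percentage read from them.
- **Death.** A condensed article may leave the handling of death to the full protocol, so its absence is weak as a separate fault. It matters here only because deaths, if censored like DDKT, add to the overstatement. If they are kept at risk to one year, they do not.
- **Size.** The wait is counted from first dialysis, not from study entry, and both newly referred and already listed patients are enrolled, so a constant hazard is a rough device. Sampling error is also of similar size: at 80 patients per arm (half of the planned 160) and 30% LDKT, the standard error is √(0.30 × 0.70/80) = 5.1 points. This stands as to magnitude. The bias nevertheless runs in one direction, and more patients would not reduce it.

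**Conclusion.** The point holds for the time-to-event graphs and for absolute LDKT proportions taken from them. If they are drawn as one minus Kaplan-Meier under the stated rule, they overstate the proportion reaching LDKT. The direction follows from the method whenever DDKT or death is censored and LDKTs follow. The size is illustrative: roughly 10-20% in relative terms (ratios of 1.09 to 1.23 in the table), or about 1-8 percentage points at 12 months. It rests on assumed constant hazards and an assumed range for LDKT, since the article gives no event rates for this population.

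The documents do not support two stronger readings. The Cox hazard ratio and the one-year counts are not invalidated. Nor does anything in the article show that DDKT or death rates differ between arms; with similar rates both curves are inflated by nearly the same factor, and the relative comparison changes little. This is a modest fault in the display of a secondary outcome, worth correcting because the correction is easy.

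**What to change.** In the Statistical analysis section:

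1. State that DDKT, and death before LDKT, are competing events for LDKT.
2. Replace the unspecified time-to-event graphs with Aalen-Johansen cumulative incidence curves by arm, and take any 12-month LDKT proportion from these.
3. Keep the Cox model with censoring at competing events, and label its result a cause-specific hazard ratio.

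A Fine-Gray model and Gray's test may be added but are optional.

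The cost is a little more analysis work on data already being taken from medical records. The LDKT percentages displayed will be slightly lower than under one minus Kaplan-Meier.
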